## Abstract

**Background:**

There is a strong evidence base for the benefits of parenting interventions for parents without severe mental illness (SMI). As the impact of maternal SMI can be significant on child development, mothers need support to maximise outcomes for themselves and their children. Some mothers with SMI require admission jointly with their baby to a Mother and Baby Unit (MBU), a psychiatric inpatient ward, for assessment and treatment. However, MBUs do not yet offer formally evaluated, evidence-based parenting interventions as a matter of routine. This paper describes a study to investigate the feasibility and acceptability of conducting a randomised controlled trial (RCT) to evaluate a parenting and psychological intervention targeting the mother’s and infant’s wellbeing for mothers admitted to a MBU.

**Methods/Design:**

This study is a multisite, single-blind feasibility trial with half the participants randomised to the Baby Triple P Positive Parenting Programme plus treatment as usual (TAU) and the other half randomised to TAU alone. Self-report and observer-rated assessments are collected at baseline, 10 weeks post-baseline and 6 months post-baseline. Participants are mothers admitted to a MBU in the Northwest of England or the Midlands. Participants are included if they are fluent in English to provide informed, written consent. Our objective is to determine whether we can recruit 66 women, randomise 60, and retain them in the intervention and study, and whether the intervention and study procedures are acceptable. As part of a nested process evaluation, qualitative interview data from trial participants and MBU staff will inform feasibility and acceptability. The feasibility of collecting data required to conduct an economic evaluation of the intervention will also be explored.

**Discussion:**

Although research has been conducted in relation to mothers with severe mental illness and MBUs, to our knowledge, this is the first controlled trial to test the feasibility, acceptability, uptake and retention alongside the potential efficacy of a parenting intervention for this population. This study is essential to examine the contextual challenges involved in this setting with this population and to identify any refinements required.

**Trial registration:**

ISRCTN12765736. Date of first registration: 2 February 2017.

**Electronic supplementary material:**

The online version of this article (10.1186/s13063-018-2869-z) contains supplementary material, which is available to authorized users.

## Background

Given the significant impact of maternal mental illness on child development [1–4], the importance of interventions to promote optimal outcomes for children in the early years has been widely recognised [5–11]. However, in order to raise infants in loving and supportive environments, parents need to feel confident in their parenting skills [12]. Parents, and especially mothers, with good parenting skills feel that they have a good parent–infant relationship. This relationship has been found to influence the infant’s wellbeing, social and academic competence, and emotion regulation abilities [1–4, 13, 14].

Parenting an infant can be a challenge for parents enjoying good mental health, but it can be an even greater challenge for parents who are mentally unwell. Maternal mental illness has profound effects on the woman, her family and children [1–4, 13, 14]. Estimates suggest that 10–20% of women develop mental health problems during pregnancy or within the first year of having a baby [11]. Furthermore, it is estimated that 1% of women have severe mental illness (SMI) or significant mental health difficulties requiring specialist psychiatric services [15, 16]; in 2013, at least 6985 of the 698,512 women giving birth required admission to a Mother and Baby Unit (MBU). Research has shown that perinatal depression, anxiety and psychosis carry an estimated total cost to society of £8.1 billion for each 1-year cohort of births in the UK [11], a cost of approximately £10,000 for each birth. Perinatal psychosis costs approximately £53,000 per case [11].

The UK has been at the forefront of developing inpatient psychiatric units to admit mothers with existing or perinatal onset SMI, jointly with their babies [17]. These mothers present with various difficulties, including (puerperal) psychosis, bipolar disorder, schizophrenia, severe affective illness (such as postnatal depression) and mother–infant relationship difficulties. The importance of specialist perinatal services in the treatment offered to these mothers and their families has been recognised [6, 8, 15, 16, 18, 19]. Despite improvements in mental illness and mother–infant interactions, as yet there are no structured parenting interventions that guide health professionals to help mothers with mental health difficulties strengthen early parenting [20, 21].

The NICE guidelines and reviews recommend psychiatric and psychological interventions for mothers with mental health problems [5–10, 19, 22], because the quality of the mother–infant relationship in mothers with severe mental health difficulties can be poorer compared to mothers with mood disorders [23, 24]. Although research has shown that treating the mother’s symptoms improves her mental health, this improvement does not necessarily directly relate to her interaction with her infant [25]. Interventions using video feedback appear to be useful in improving the mother–infant interaction in mothers with severe mental health difficulties [26, 27], but video feedback focuses only on interactions and, as yet, this intervention has not been shown to be effective for mothers admitted to a MBU. Therefore, there is a need for further research on parenting interventions with a skills training component for mothers who are looking after babies and who experience SMI or severe mental health difficulties (e.g. severe depression or postpartum psychosis) [20, 28].

Parenting interventions help parents learn how to provide appropriate emotional and physical care, so that children can thrive and reach their full potential [29]. Although parenting programmes improve the emotional and behavioural adjustment of children and parental psychosocial wellbeing [30–32], the importance of addressing parenting issues as well as parental mental health needs has been emphasised [33, 34]. Certainly, mentally ill mothers are not inherently poor parents. Indeed, a review and meta-synthesis of 23 studies has identified the importance women with severe mental health difficulties attach to motherhood [35]. However, mothers have expressed that the demands associated with parenting whilst at the same time coping with significant mental health difficulties are considerable [36].

Parenting competence and confidence help parents to balance parenting demands with their own needs [37]. A Dutch study reported increased parental self-efficacy following participation in a parenting intervention for parents with severe mental health difficulties, but these were not parents of infants (less than 12 months old) [34]. Effective interventions focusing on the parenting needs of mothers with significant mental health difficulties, who parent their babies, are needed [20, 33, 38].

### Positive parenting programme

The Triple P system of interventions has impressive theoretical, scientific and clinical foundations [39–43]. Its aims include (1) enhancing parental knowledge and resourcefulness, (2) promoting nurturing, low-conflict environments for children, and (3) promoting children’s social, emotional and intellectual competencies through positive parenting practices.

The Triple P framework offers accessible, multi-level interventions increasing in intensity for parents with different needs, regardless of sociocultural differences, age and gender [39]. Triple P has recently been expanded to families with children aged under 1 year, which provides an opportunity to test the intervention with mothers with severe mental health difficulties.

The Baby Triple P Positive Parenting Programme, designed to be an intervention at level 4 of the Triple P hierarchy of five levels, has been developed to enhance parental knowledge, skills and confidence. It targets three important areas crucial in enhancing maternal and infant wellbeing, namely (1) positive parenting skills promoting secure attachment, reducing maternal and infant distress, (2) improving partner and social support to increase maternal and overall family wellbeing and (3) increasing maternal coping resources to reduce mental health difficulties. Its primary focus is on enhancing maternal parenting competence and confidence, thereby improving the quality of the mother–infant relationship and subsequent attachment, which in turn improves infant and maternal wellbeing.

### Baby Triple P Positive Parenting studies

In preparation for this feasibility study, the chief investigator has led a number of studies related to Baby Triple P. For example, a small pilot study examined the feasibility and acceptability of Baby Triple P in mothers with postnatal depression [44]. The results were in the predicted direction regarding level of happiness, self-regulation, subjective bonding and depression (at post-treatment only). The 12 women who received Baby Triple P completed all sessions, were retained for all follow-up assessments and rated it as highly acceptable.

A second study explored the views of mothers admitted to the Manchester MBU about the perceived acceptability and feasibility of a parenting intervention like Baby Triple P in the setting of a MBU. Using Q-methodology, which is designed to assess opinions and views, all participants agreed on the perceived benefits of Baby Triple P and the MBU environment as suitable to facilitate it. The intervention was viewed as an acceptable and feasible parenting intervention [45]. However, without staff support, the possible implementation of this intervention on the MBU would be difficult. Consequently, we conducted another study with MBU staff [46], which showed that staff also regarded this intervention to be feasible and acceptable for the MBU setting. MBU staff indicated that the intervention could help reduce the ‘bad parent’ stigma often identified in the population of mothers presenting with severe mental health difficulties [35].

Given these encouraging findings, we aim to test the feasibility and acceptability of conducting a randomised controlled trial (RCT) to evaluate the Baby Triple P programme plus treatment as usual (TAU) in mothers with severe mental health difficulties admitted to one of two UK National Health Service (NHS) MBUs. Qualitative data from MBU staff and participants will be used to (1) assess the acceptability of the intervention and RCT procedures and (2) allow the refinement of the approach and intervention in preparation for a larger clinical trial. The overall aim of this feasibility study is to evaluate the Baby Triple P intervention in mothers with severe mental health difficulties in a MBU setting. The objectives of this feasibility RCT are:To examine the feasibility of the design and procedures of a future RCT.To examine the acceptability (to mothers and MBU staff) of the design and procedures of a future RCT.To examine the key cost indicators associated with the intervention.To involve service users to guide and inform the research.To examine the feasibility of (1) the recruitment methods (through the MBU ward staff and consultant psychiatrist), (2) recruiting sufficient numbers of mothers to be able to estimate an effect size for a future RCT, (3) the randomisation procedures in inpatient ward settings, (4) engagement and retention of mothers in the study (including completion of outcome measures) and (5) piloting data collection procedures (including frequency, duration and format of assessments).To examine mothers’ and MBU staff acceptability of Baby Triple P.To determine the best strategies to avoid or minimise possible contamination (e.g. mothers sharing the Baby Triple P workbook with mothers in the TAU group) or log such incidences.To assess the fidelity of Baby Triple P delivery on the MBU.To determine factors associated with engagement of mothers in and adherence to Baby Triple P.To examine attrition rates and causes and explore solutions to attrition.To determine the suitability of the primary and secondary outcomes and their respective measures for a future RCT alongside appropriate follow-up assessment time points.To explore the key cost elements and the appropriateness of the five level EQ-5D (EQ-ED-5 L) as a measure for a calculation of utility of the intervention in this population.

We aim to (1) establish whether the study procedures work and are acceptable to participants and staff so that a future full-scale trial and economic evaluation can follow and (2) explore whether the intervention is perceived to be beneficial in improving maternal parenting confidence, mood and other psychological symptoms, quality of life and mother–baby bonding.

## Methods/Design

### Preliminary pilot work

We conducted two studies to investigate patient (*n* = 15) and staff (*n* = 16) views and opinions regarding the acceptability of an intervention like Baby Triple P being offered on a MBU [45, 46]. These findings alongside information from a pilot study of Baby Triple P offered to mothers with postnatal depression [44] and patient and public involvement consultations were used to inform the treatment and implementation protocol of this RCT.

### Trial design

Following the Medical Research Council framework for the development and evaluation of complex interventions [47], this study includes quantitative and qualitative assessment of feasibility and acceptability. It is designed as an individually randomised, multisite, parallel- group, single-blind (outcome assessors) feasibility RCT comparing a parenting intervention (the Baby Triple P Positive Parenting Programme) plus TAU with TAU alone. The trial was designed to be individually randomised because the small number of MBUs would not permit cluster randomisation in a future definitive trial. To mitigate against contamination, participants randomly allocated to the intervention will be asked not to share the intervention workbook and any other information learnt during sessions with other mothers on the MBU. Figure 1 provides an overview of the trial design based on CONSORT guidelines [48], whilst Fig. 2 shows a schedule of study enrolment, interventions and assessments. The recommendations for interventional trials (SPIRIT) checklist [49, 50] is available as Additional file 1.

**Fig. 1 Fig1:**
[figure not shown]
CONSORT diagram showing study design

**Fig. 2 Fig2:**
[figure not shown]
Schedule of enrolment, interventions and assessments

Assuming a drop-out rate of 10% between recruitment and randomisation in an inpatient setting, a maximum of 66 participants will be recruited and a maximum of 60 will be randomised after completion of baseline measures during their inpatient admission to a MBU. Participants will be randomly allocated, using an independent Clinical Trials Unit (CTU), to TAU or to TAU plus eight sessions of Baby Triple P. Additional sessions can be offered, for example, to conduct an initial assessment and, if required, the intervention can be delivered more flexibly.

Participants are followed up at 10 weeks post-baseline and at 6 months post-baseline. The end of treatment is not fixed but dependent on progress and participants’ capacity to engage, whereas assessment time points are fixed.

### Trial setting

This feasibility study is being conducted in two MBU located in the North West of England and the Midlands, England, UK. MBUs are inpatient psychiatric units for mothers who are admitted jointly with their babies and who require psychiatric nursing care [8, 51]. MBUs in England are commissioned by NHS England. They typically have 4–12 beds and are staffed by specialist perinatal mental health staff, including psychiatrists, nursery nurses, psychiatric nurses and clinical psychologists. Average admission to MBUs in the UK is 7 weeks, ranging from 4 to 12 weeks [21]. The two MBUs are comparable in terms of size and staffing. Both MBUs are located in large cities with socially and ethnically diverse populations.

### Ethics and governance

This trial is supported by the National Institute for Health Research ‘Research for Patient Benefit Programme’ (NIHR RfPB, grant number PB-PG-1014-3505) and sponsored by the University of Manchester (16233). The study has been approved by the NHS National Research Ethics Service via the North West – Greater Manchester South Research Ethics Committee (REC reference number 16/NW/0510). It is conducted following the Good Clinical Practice guidelines in accordance with the principles of the Declaration of Helsinki. The study also has Health Research Authority approval (IRAS project number 188486, protocol number 16233) and Research and Innovation approval by both NHS trusts overseeing the two participating MBUs (e.g. Greater Manchester Mental Health NHS Foundation Trust and Birmingham and Solihull Mental Health NHS Foundation Trust). Trial monitoring is carried out via the Manchester CTU and the trial is also overseen by an independent Trial Steering and Data Monitoring Committee consisting of academics, clinicians, a service user and an independent statistician. Through regular meetings, these committees will be informed of any adverse events and protocol modifications. Procedures are in place to promote data quality (e.g. by ensuring data coded and entered into databases are double checked, etc.). Personal data will be kept confidential and information will be anonymised in the datasets, which will be accessed by the immediate research team only.

Various aspects of the study, such as the wording in participant information sheets and future dissemination plans, will also be informed by our service user group (or Patient and Public Involvement group). This service user group consists of up to six mothers with past experiences of severe mental health problems and/or inpatient admission to a MBU.

### Inclusion and exclusion criteria for participants

Participants are women who are either pregnant or admitted jointly with their infant to a MBU for the assessment and treatment of their severe mental health problems. As the intervention was designed to be universally applicable to parents and caregivers, all eligible participants can take part irrespective of their admission status (voluntary or involuntary, i.e. detained under the Mental Health Act) and their current baby care. Participants are eligible to take part if they are aged 18 or over, have at least one infant aged from 0 to 12 months who they parent or are going to parent, or if they are in the third trimester of pregnancy and are expected to reside on the MBU following delivery. Participants have to be able to comprehend and understand English and provide written informed consent.

Participants are excluded if their discharge has been scheduled within 7 days from the date of recruitment or if their infant will be removed from their care on a non-temporary basis. Participants whose current symptoms seriously compromise their ability to concentrate on the assessments or intervention sessions or who show severe personality disorder traits, including significant self-harming behaviours (such as attempting suicide), will not be considered for inclusion until their symptoms have stabilised as judged by their psychiatric team.

### Nested process evaluation: inclusion and exclusion criteria for participants and staff

As part of a nested process evaluation, we will undertake a qualitative study of staff and patient experiences and views of Baby Triple P and a sample of participants (*n* < 15 women and *n* ≥ 15 MBU staff) will be interviewed. Interviews will explore participants’ and MBU staff experiences and expectations of the study procedures and the intervention alongside its content. Facilitators and barriers to implementation of this type of intervention within a MBU setting will be identified.

Participants (*n* < 15) who were allocated to the intervention arm plus TAU, irrespective of subsequent intervention engagement, will be asked to take part in interviews for the nested qualitative aspect of this study. The same inclusion and exclusion criteria as above will apply.

MBU staff participants (*n* ≥ 15) will also be recruited if they are permanent full-time or part-time members of the MBU staff team and have worked on the MBU for at least 6 months. Psychiatry and medical MBU staff will also be recruited if they have worked on the MBU for at least 4 months. Separate participant information sheets and consent forms for this aspect of the study will be used; similar consent procedures outlined below will apply.

### Recruitment and consent procedures

Recruitment is over an 18-month period from November 2016. Posters are displayed on the MBU to alert potentially eligible patients that this study is being undertaken. MBU staff also identify eligible patients and offer them a Consent to Approach form (a form which gives written consent for the research team to approach patients with information about the study) to sign if they are interested in hearing more about the study. Eligible patients who provide consent (to be approached by the research team) are then approached in person by the researcher who (1) provides them with a Participant Information Sheet outlining the study procedures and requirements, (2) explains the research to them and (3) gives them the opportunity to ask questions. Eligible patients are required to take at least 24 h to think about whether they would like to take part in the feasibility trial. As the MBU is an inpatient psychiatric unit, some participants may require more time to consider their participation, and this will be allowed. After 24 h, or when participants indicate that they are ready to discuss their possible participation further with the researcher, or if the participant is happy to take part, written informed consent is obtained. If they do not wish to take part, they are thanked for their time and asked if they are happy to share their reason for not wishing to take part, but are not obliged to do so. Furthermore, the project manager checks for continued consent with participants when (1) informing participants which arm they have been allocated to, (2) when patients are discharged from the ward, and (3) before and at the beginning of follow-up assessments. A copy of the consent form is given to the participant to keep, one is placed in the clinical notes and another in the investigator site file. Consent forms are retained as records.

After participants have provided written consent to take part in the study, we ask them to complete a Consent to Contact form and to provide their email addresses and telephone numbers so that the research team can contact them (1) to remind them of any study assessment or intervention appointments or interview times, (2) to forward a summary of the findings if they indicate on the consent form that they wish to receive this and (3) to contact them about taking part in other studies within the programme of research if they indicate on the consent form that they agree to this.

Each participant has the right to withdraw from the study at any time. In addition, the research team may decide to discontinue a participant from the study at any time if this is deemed to be necessary for one of the following reasons: ineligibility (either arising during the study or retrospectively), significant protocol deviation, significant non-compliance with the study requirements, withdrawal of consent and loss to follow-up. The reason for withdrawal will be recorded if participants are happy to share this but they are not obliged to do so.

All participants are reimbursed at the end of the study with £30 to thank them for their time and contributions. They are also offered a certificate and a list of useful contacts/organisations for additional support.

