### Outcomes and measures

Outcomes relate to uptake (the proportion of eligible participants consenting to partake), attrition and retention rates. Through semi-structured interviews with participants and MBU staff we will also further explore the acceptability of the study procedures and intervention. We will assess the feasibility and acceptability outcomes as follows:Feasibility of recruitment will be measured through recording how participants found out about the study, recruitment rates, number of potential participants found eligible, initially approached by MBU staff, consented to be approached by the research team, and approached about the study by the research team, reasons for declining to be approached or take part in the study if known, and percentage of eligible participants consented and their characteristics.Feasibility of randomisation will be assessed by recording number of refusals to be randomised.Engagement/retention in the study and to study procedures will be measured by recording the number of participants who withdraw and the time point at which they withdraw from the study. Reasons for leaving the study early will be recorded if known. The number of participants who complete outcome measures at each of the time points and the completeness of their data will be recorded.Engagement/retention in the intervention will be measured by recording the percentage of intervention sessions delivered, duration and maternal self-reports of time spent between sessions on Baby Triple P as well as maternal use of the workbooks. Reasons for leaving the intervention early will be recorded if known.Acceptability of the intervention and study design and procedures will be assessed post-intervention via a questionnaire (for acceptability of the intervention only) and semi-structured interviews with participants allocated to receive Baby Triple P plus TAU (*n* < 15) and MBU staff (*n* ≥ 15).

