### Data analysis

Participant flow will be reported in accordance with the CONSORT statement (Fig. 1). Baseline data will be described using summary statistics (means and standard deviations or numbers and percentages). The feasibility findings will be tabulated and associated graphical summaries of the key indicators of success will be presented. All anonymised participant data will be included in the efficacy analysis using an intention-to-treat approach.

Data from clinical outcome measures will be analysed using a linear regression model, allowing for baseline measurements of outcome, treatment assignment and NHS trust as covariates, at each assessment point separately. We will report 95% CIs and point estimates for effects instead of *p* values. The results will be used to provide an indication of the population effect size required for a future full-scale definitive trial. However, as a feasibility RCT, this study is not powered to find an effect.

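### The research team may discontinue randomised women from the study itself, which is in tension with intention-to-treat and makes retention partly a team decision

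*Protocol article*

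**What the plan says.** Recruitment and consent procedures first gives every participant the right to withdraw. It then adds a separate power: "the research team may decide to discontinue a participant from the study at any time if this is deemed to be necessary". The grounds are "ineligibility (either arising during the study or retrospectively), significant protocol deviation, significant non-compliance with the study requirements, withdrawal of consent and loss to follow-up". On recording, the same paragraph says only "The reason for withdrawal will be recorded if participants are happy to share this but they are not obliged to do so".

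Outcomes and measures opens with "Outcomes relate to uptake (the proportion of eligible participants consenting to partake), attrition and retention rates". Engagement and retention in the study is to be measured by "recording the number of participants who withdraw and the time point at which they withdraw from the study". The same item also records reasons for leaving early where known, how many women complete the measures at each time point, and how complete their data are. Retention in the intervention is a separate item.

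Data analysis states "All anonymised participant data will be included in the efficacy analysis using an intention-to-treat approach". The model is a linear regression "allowing for baseline measurements of outcome, treatment assignment and NHS trust as covariates, at each assessment point separately".

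**The concern.** The clause concerns leaving the study, not leaving Baby Triple P, and it applies at any time. Of the five grounds, withdrawal of consent is the woman's own act. The other four can be applied to a randomised woman without any decision of hers, and three of them (ineligibility, deviation, non-compliance) are team judgements. All four can arise after randomisation and may be related to prognosis. For example, permanent removal of the infant from the mother's care is an exclusion criterion, and it could come about during follow-up.

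Two things are at stake. The first is the effect estimate. If discontinuation ends outcome collection, the women analysed at 10 weeks or 6 months are no longer all those randomised, and they have been selected by what happened after allocation. The second matters more in a feasibility trial. Attrition and retention are outcomes in their own right, and the objectives include examining the rates and causes of attrition. A figure that mixes women who chose to leave with women whom the team closed out does not answer that question. Follow-up that was never sought cannot be recovered at analysis.

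**Working it through.** **Sections side by side**

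1. Discontinuation is from the study, at any time, by the research team (Recruitment and consent procedures). Nothing there says that outcomes are still sought afterwards.
2. The regression is fitted at each assessment point separately (Data analysis). A woman discontinued before 10 weeks contributes to neither follow-up model; one discontinued between 10 weeks and 6 months contributes to the first only.
3. The intention-to-treat sentence covers all participant data. It protects what has been collected and cannot supply an outcome that was not.
4. The retention item counts women who withdraw. It does not say whether a team-initiated discontinuation counts as a withdrawal, or whether such a woman stays in the denominator.

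**Inputs**

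- At most 66 recruited and 60 randomised, assuming 10% drop-out before randomisation (Trial design). The stated 66 is reproduced by 60 × 1.10 = 66; dividing instead gives 60/0.90 = 66.7, or 67. The point does not depend on this difference.
- 1:1 allocation (Randomisation), so about 60/2 = 30 per arm.

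**Effect of one removal on retention**

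- Overall: 1/60 = 1.7 percentage points.
- Within one arm: 1/30 = 3.3 percentage points.

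**Illustration**

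The article gives no loss or removal counts. Assume 6 participant-driven losses among 60 and vary the number of team removals, k. Retained = 60 − 6 − k; intervals are Wilson 95%.

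| Team removals (k) | Retained / all randomised | 95% CI | Retained / (60 − k) |
|---|---|---|---|
| 0 | 54/60 = 90.0% | 79.9 to 95.3 | 54/60 = 90.0% |
| 3 | 51/60 = 85.0% | 73.9 to 91.9 | 51/57 = 89.5% |
| 6 | 48/60 = 80.0% | 68.2 to 88.2 | 48/54 = 88.9% |

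With 6 removals, the same trial could report 80.0% or 88.9%, depending on a denominator that the article does not fix.

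**Effect estimate**

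If a fraction f of one arm is removed and the removed women score D standard deviations (SD) worse than those who remain, that arm's mean shifts by f × D. With f = 0.10 to 0.20 (3 to 6 of 30) and D = 0.5, the shift is 0.05 to 0.10 SD. Both f and D are assumptions. The sign depends on which arm loses the women, and equal removals of similar women in both arms would cancel. For comparison, the unadjusted 95% CI half-width with 30 per arm is 1.96 × √(2/30) = 0.51 SD.

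**The case against.** The strongest reply is that the discontinuation clause governs participation while Data analysis governs the analysis set, and the latter commits to intention-to-treat on all data. That stands as far as it goes. A reader might infer that the clause breaks intention-to-treat or discards women from the analysis. The article does not support this: no section deletes or excludes a discontinued woman's data. What remains is the practical consequence that no later outcome exists to include.

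A reader might also infer that removals would fall mainly on the intervention arm, because only that arm has sessions to miss, and so favour Baby Triple P. The text does not support this either. The ground is non-compliance with study requirements, which apply to both arms. Retention in the study and in the intervention are kept apart, delivery is flexible, and intervention-arm women are invited to interview whatever their engagement. Nothing links missed sessions to removal from the study.

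Nor does the article say that one missed 10-week assessment counts as loss to follow-up or ends the 6-month approach. Because loss to follow-up is listed as a ground, this should be made explicit, but it is not a stated rule.

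The retention item is fuller than a count of withdrawals. Completion at each time point and participant flow under CONSORT will also be reported, which would make some of the loss visible. They do not by themselves show who decided that a woman should leave.

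Finally, this is a condensed article, and the full protocol or analysis plan may settle the handling of discontinued women. Silence on such detail is no fault. The point rests on the rule that the article does state, which as worded removes women from the study.

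**Conclusion.** The point holds as a tension between stated rules, at moderate severity. The clause covers randomised women and concerns the study, not only the intervention. Followed as written, it would leave some women without outcomes for reasons that arise after randomisation. It also makes a main feasibility outcome depend partly on team decisions, at about 3.3 percentage points of an arm's retention per removal.

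This rests on two assumptions: that the power is used after randomisation, and that discontinuation from the study carries its ordinary meaning that outcomes are no longer sought. The retention percentages in the table are illustrations on assumed counts.

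Neither the direction nor the size of any bias in the effect estimates can be derived from the article. The assumed 0.05 to 0.10 SD is small beside an interval half-width of about 0.5 SD, in a trial that says it is not powered to find an effect and reports intervals instead of p values. The case for a change therefore rests mainly on retention and on follow-up that cannot be recovered later, and it does not reach must-fix.

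**What to change.** Reword the clause in Recruitment and consent procedures so that, after randomisation:

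- Later or retrospective ineligibility, protocol deviation, non-compliance and loss of contact are recorded with date and reason, but the 10-week and 6-month outcomes are still sought and the woman is analysed in her allocated arm.
- The exceptions are withdrawal of consent and consent found never to have been valid. The second is needed because ability to give informed consent is itself an eligibility criterion.
- A missed 10-week assessment does not stop the 6-month approach.

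In Outcomes and measures, report retention with all randomised women as the denominator. Tabulate participant withdrawal, team-initiated discontinuation and non-contact separately by arm. The reason for a team-initiated discontinuation should always be recorded, since it does not depend on what the woman chooses to share.

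If the full protocol already says this, the clause need only be aligned with it. The cost is wording and a few extra contact attempts, and the article already allows assessment in person, by telephone or by post. Trial status says that recruitment was still under way, so the change could take effect for women yet to be followed up. It does not affect any decision on whether or when the intervention is stopped.
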